## Abstract

**Background:**

Chronic Kidney Disease (CKD) is associated with reduced muscular strength resulting in profound fatigue. The physiopathology of these changes, their prevalence and evolution are still debated. Moreover, we have little data on elderly CKD patients. The present study protocol aims to 1) quantify the prevalence of low muscle strength (dynapenia) in a cohort of elderly patients with advanced CKD and to 2) characterize their force production coupled with electromyographic features and the symptoms of fatigue compared to a matched control group.

**Methods:**

This is a case-control, prospective, interventional study. Inclusion criteria: age ≥ 60 years; CKD Stage 3b-5; clinical stability (i.e. no hospitalization and ≤ 25% in creatinine increase in the previous 3 months). Controls with normal kidney function will be matched in terms of age, gender and diabetes mellitus (requisite: estimated glomerular filtration rate ≥ 60 ml/min/1.73m^2^ available in the last 6 months). Exclusion criteria for cases and controls: neuromuscular disease, life expectancy < 3 months.

The handgrip strength protocol is an intermittent test consisting in 6 series of 9 repetitions of 3-s sub-maximum contractions at 40% of the maximum voluntary contraction (MVC) and 2 s of resting time between contractions. Each series is separated by one fast sub-maximum contraction and one MVC. Strength is assessed with a high-frequency handgrip dynamometer paired with surface electromyography. Symptoms of fatigue are assessed using MFI-20 and FACIT-F questionnaires. In order to reach a statistical power of 96%, we plan to enroll 110 subjects in each group.

**Discussion:**

The novelty of this study resides in the application of an already validated set of tests in a population in which this combination (dynamometer, electromyography and questionnaires) has not previously been explored. We expect a high prevalence of dynapenia and a higher fatigability in CKD patients. A positive correlation is expected between reported fatigue and fatigability.

Better appreciation of the prevalence and the relationship between fatigability and a sensation of fatigue can help us target interventions in CKD patients to improve quality of life and survival.

**Trial registration:**

The study was approved by Ethical Committee EST III n°20.03.01 and was recorded as a Clinical Trial (NCT04330807) on April 2, 2020.

## Background

Chronic kidney disease (CKD) is defined as a structural or functional abnormality of the kidneys that has lasted at least 3 months and has implications for health [1]. The kidneys have a major role in the maintenance of homeostasis, ensuring water and electrolyte balance that directly determines the functioning of vital organs. It is for this reason that a decline in kidney function induces a number of systemic metabolic alterations, especially in the most advanced stages i.e., glomerular filtration rate (GFR): ≤45 ml/min/1.73m^2^ [2].

Among the symptoms associated with advanced CKD, fatigue is often reported by patients, with a prevalence ranging between 50 and 70% [3]. Fatigue is defined as a subjective sensation of weakness, increasing sense of effort, mismatch between exerted and actual effort [4]. Fatigue, which has a remarkable impact on a patient’s everyday activities and quality of life, can be subjectively evaluated using validated questionnaires.

The pathogenesis of fatigue is complex. Fatigue can arise from disease-related issues (e.g., diffuse vascular disease, anemia, changes in lifestyle habits), psychological conditions (e.g., stress, depression, sleep disorders) and pathophysiological changes (e.g., decline in aerobic capacity or muscle strength) [5]. These problems are common in other chronic diseases, such as the consequences of stroke [6], cancer [7, 8], multiple sclerosis [9], rheumatoid arthritis [10, 11] and diabetes mellitus [12–15]. In all of them, observed neuromuscular changes are associated with fatigue [16].

Neuromuscular fatigability is defined as a reduction in the patient’s muscular ability to perform a standardized task [17]. In general, inability to exert the desired force is not restricted to muscle-mass decline. Several factors concur to determine muscle function: fiber type (i.e., slow or fast twitches), metabolism (i.e., aerobic or anaerobic), presence of fat infiltration or fibrosis and interactions at the neuromuscular junction [18]. CKD induces chronic muscle function changes [19–21]: this is relatively well documented for dialysis patients [22, 23], but we still have little data about the loss of muscle strength (dynapenia [24]) in CKD patients.

In the course of chronic dialysis, the loss of muscle function is worsened by several factors, such as acidosis, loss of amino acids (up to 12 g per hemodialysis session or 4 to 6 g per day on peritoneal dialysis) and/or the presence of anorexia. In this context, the loss of strength is mainly attributable to a decrease in muscle-mass, characterized by the loss, or a decrease in size, of the contractile units [25–27]. Conversely, changes in the excitation-contraction coupling system have been little explored and are poorly understood, especially in patients with advanced CKD.

The grip isometric analysis (i.e., handgrip) is the most commonly used test to assess strength in patients who have advanced CKD [28]. The handgrip test is simple and rapidly performed; it yields reproducible results and can easily be integrated into routine clinical practice. In CKD patients, this test demonstrates a close correlation with survival, nutritional status and quality of life [29–33]. Moreover, an isometric contraction is less traumatic than a dynamic contraction [34]. Finally, a handgrip is a simple routine gesture and does not usually cause pain.

Thus, the aim of the study is to assess the neuromuscular features of elderly patients with advanced CKD and symptoms of fatigue coupled with dynapenia. To our knowledge, this is the first study to apply a complex set of validated tests to a large population of elderly patients who have advanced CKD but are not on dialysis, with respect to an age, sex and diabetes matched control group. The research will highlight neuromuscular features associated with dynapenia in elderly CKD patients. In addition, the relationship between dynapenia and subjective fatigue will be analyzed to identify novel therapeutic interventions. These findings will be rapidly translated into clinical practice, with a view to adapting physical activity programs to improve neuromuscular function in the management of CKD symptoms.

## Methods

### Aims

The primary objective of this trial is to define the prevalence of dynapenia in elderly CKD Stage 3b-5 patients. This will be achieved through the analysis of handgrip strength.

The secondary objective is to define the characteristics of dynapenia in elderly patients with advanced CKD during a standardized task considering:
the evolution of MVC;the evolution of the discharge frequency of motor units;motor-unit recruitment ability;the evolution of the delay between the nervous stimulus and contraction;the relationship between dynapenia and subjective fatigue.

### Clinical implications

By shedding light on the specific characteristics of dynapenia and its link with a patient’s sense of fatigue and fatigability [4], the PIONEER study intends to guide the management of adapted physical activities recommended by academic associations.

### Study design

A case-control, interventional, prospective study.

### Setting of study

The study will be carried out in Le Mans hospital (France), in the outpatient unit for the care of advanced kidney disease (UIRAV, Unité pour l’Insuffisance Rénale chronique AVancée). The UIRAV unit follows about 210 patients which are not on dialysis (90% over the age of 60), whose mean age is 74 years; 60% are males and diabetes mellitus prevalence is approximately 50%. Of these, 180 patients are followed for CKD Stage 3b-5. As previously described by Fois et al. [35], UIRAV’s main objective is to offer frequent follow-up and to delay the start of dialysis. The frequency of controls is based on CKD stage and overall clinical stability. For example, patients with stable kidney disease Stage 3b are seen every 8 to 12 weeks, while patients with CKD Stage 5 are seen at least once a month. Study proceedings is described in Fig. 1.

**Fig. 1 Fig1:**
[figure not shown]
Flowchart of the study. INC: inclusion criteria; EXC: exclusion criteria

### Definition and measures

#### Dynapenia

Dynapenia is an age-associated loss of muscle strength that is not caused by neurologic or muscle diseases [24]. In our study, dynapenia will be diagnosed if the mean of three MVC after a brief warm up, is lower than the reference value matched for age and sex. The study by Ramírez-Vélez et al. [36] will provide reference values for elderly patients.

#### Fatigability

Fatigability is defined as a reduction in the patient’s muscle performance on a standardized task [17]. Fatigability, which is an indicator of objective fatigue, is evaluated by measuring critical force (F_crit_) during a standardized task. The F_crit_ value corresponds to the asymptotic value of the last stable part of the MVC evolution curve (Fig. 2) [37]. F_crit_ is the maximum exercise intensity that a subject can produce in a given metabolic environment, in other words, it identifies the threshold at which fatigability develops [38].

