**Fig. 2 Fig2:**
[figure not shown]
Fatigability protocol with handgrip and EMG acquisition. **a** Neuromuscular fatigability protocol: the green box represents the warm-up period, lasting a maximum of 1.5 min; the orange arrows are FSC; the blue lines are MVC and the purple lines are contractions at 40% of MVC. The red points represent the maximal forces awaited allowing critical force determination, while the evolution is represented with a red spotted line. Rest duration is 20 s (*), 2 min (nos. 1 and 2), 5 min (no. 3), 1 min (no. 4), 2 min (no. 5) and 3 min (no. 6). **b** Parallels between the 40% MVC contractions required and the muscle activation signals recorded. FSC: fast sub-maximum contraction; MVC: maximum voluntary contraction

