**Fig. 3 Fig3:**
[figure not shown]
Set-up of the study and standardized position

Preparing the arm for placement of the electrodes will include shaving the skin and cleaning the area hosting the four recording electrodes [43, 44] with a sponge and alcoholic disinfectant to reduce impedance. Electrodes will be placed over the flexor digitorum superficialis muscle belly along the fiber direction while following international SENIAM recommendations and the four electrode positions previously described [43–45].

The exercise, illustrated in Fig. 2, will begin with a warm-up, to familiarize the person with the instruments and situation, at a slow and comfortable pace not exceeding 1 min and 30 sec. The warm-up will consist of dynamic extensions of the hand and fingers: an extension at maximum speed, and a slow and constant flexion of the wrist and fingers. Dynamic stretches have been shown to prepare the nervous system, increase muscle temperature and improve the sensitivity of the connecting bridges between actin and myosin [46] compared to passive stretches, which can be somewhat deleterious in terms of muscle performance [47].

According to the recommendations of Maffiuletti et al. [48], fast sub-maximum contractions (FSC) should be separated from MVC to limit central inhibition. Thus, to determine the baseline FSC, five contractions at maximum speed will be performed with a twenty-second rest interval between them. The objective of these contractions is to determine the rate of force development.

As recommended by De Luca [49], patients will perform three MVC interspersed by a two-minute rest and the mean of the three contractions will be calculated. Each MVC has to be reached progressively in less than 3 sec and least 5 sec [50]. A five-minute break is scheduled after the MVC because the subsequent part of the trial is the beginning of the fatigability protocol.

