The fatigability assessment phase begins with nine contractions at 40% of MVC [51], each lasting 3 sec, followed by an FSC and an MVC. All the contractions are exerted at two-second intervals. This cycle of eleven contractions will be repeated six times. If a patient cannot maintain the 40% required force, the threshold time will be recorded without stopping the test. At the end of these cycles, the patient will rest for 1 min. Then, in order to assess their recovery capacities, the last part of the test will be administered, consisting in three series of one FSC and one MVC, separated by two- and three-minute intervals, respectively.

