### Statistical analysis

Sample size calculation was based on the results of the handgrip strength test of Lin et al. [52], who analyzed a relatively large cohort of elderly patients suffering from CKD in 2019, and the handgrip strength reference values of Ramírez-Vélez et al. [36], who analyzed a larger population of elderly patients without CKD, stratified by age and sex. With an 8% (±16%) difference, accepting a 5% alpha risk, 96% statistical power will be reached by enrolling 110 CKD patients and 110 control subjects. Considering the number of patients followed in the UIRAV unit (i.e., approximately 180 older than 60), we should be able to enroll the participants within 1 year.

Signal filtering and analysis will be performed with Matlab 2018a v9.4 (The MathWorks Inc., Natick MA, USA) and statistical analysis will be performed with SPSS v14 (IBM Corp., Armonk NY, USA). Group comparison for normally distributed variables will be assessed by means of the analysis of variance (ANOVA) or the unpaired Student T-Test. For non-normally distributed variables the Kruskal-Wallis or the Mann-Whitney Test will be used. In addition, the chronological variables (e.g., evolution of the MVC during the test) will be analyzed by mixed models with fixed effect or ANOVA with repeated measures if the test prerequisites are satisfied (normality, homoscedasticity and sphericity).

Qualitative data will be compared with the Chi^2^ or the McNemar Test.

Correlation analyses will be performed with the Pearson Test. Logistic or multiple regressions will be performed to assess the effect of different variables on the outcomes: age, sex, body mass index, stage of renal disease, diabetes mellitus, MIS and CCI (either continuous or dichotomized) as well as biochemical data. A *p* < 0.05 will be considered statistically significant.

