## Discussion

This study aims to quantify the prevalence of force decline in elderly patients affected by advanced CKD and to identify alterations at the level of the neuromuscular junction. The strength of this study is that it will be, to our knowledge, the first study to assess, in this “pre-dialysis” population, the prevalence of dynapenia coupled with an EMG recording to objectivate electromyographic fatigability features. It will also be the first trial combining an objective (i.e., F_crit_) and a subjective (i.e., FACIT-F and MFI-20) approach to assess fatigue in this population. The link between neuromuscular alterations and greater fatigue is in fact poorly understood [16], especially for CKD patients.

A higher prevalence of dynapenia is expected in the CKD population compared to the control group, with the highest prevalence in those with diabetes mellitus. Patients with diabetes appear to have decreased muscle functions [53, 54], but this result has been questioned [55]. We expect different neuromuscular features in CKD patients, specifically for F_crit_. CKD has been associated with difficulty in performing a standardized task but the origin of this disturbance (e.g., difficulty adapting the motor-unit discharge or difficulty recruiting the motor unit) is far less clear [48]. Our study will allow us to investigate these issues and clarify the underlying pathophysiological mechanisms. The temporal difference between the onset of the EMG signal and force production, i.e. the electromechanical delay, will be assessed during the FSC. We expect an increase in this delay, highlighting an alteration between the electrochemical process (i.e., synaptic transmission, propagation of the action potential, excitation-contraction coupling) and contractile and structural elements. A positive correlation is expected between subjective fatigue and objective fatigability.

The frailty of the elderly CKD population demands careful attention to the methodology employed, explaining the choice of this sub-maximum protocol to reduce as far as possible causing pain while inducing sufficient fatigue in this fragile population.

Better comprehension of the neuromuscular features of dynapenia and a deeper understanding of the relationship between fatigability and fatigue can help us guide interventions for elderly patients suffering from advanced CKD, with the final goal of targeting interventions to effectively improve quality of life and reduce morbidity.

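### Fatigability is defined as a reduction but measured by critical force, an end level not referred to baseline MVC, so expected weakness in CKD can show up as fatigability

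*Protocol article*

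**What the plan says.** Under Definition and measures, the Fatigability section opens with "Fatigability is defined as a reduction in the" patient's performance on a standardized task. It then states that fatigability "is an indicator of objective fatigue, is evaluated by measuring critical force", and that the F_crit "value corresponds to the asymptotic value of the last stable part of the MVC evolution curve". The legend of Fig. 2 says what feeds it: "The red points represent the maximal forces awaited allowing critical force determination".

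The Intervention section supplies a baseline. Three MVCs are made before the fatiguing task and "the mean of the three contractions will be calculated". The load is individualised: "The fatigability assessment phase begins with nine contractions at 40% of MVC". No section divides F_crit by that baseline, subtracts it from it, or adjusts for it.

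The Discussion treats F_crit as the objective measure of fatigue beside the two questionnaires and expects it to differ in CKD. It adds: "A positive correlation is expected between subjective fatigue and objective fatigability". On method, the Statistical analysis section says "Correlation analyses will be performed with the Pearson Test". It lists regression covariates (age, sex, body mass index, renal stage, diabetes, MIS, CCI and biochemistry), and baseline MVC is not among them.

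**The concern.** A reduction compares an end with a start. An asymptote is only the end. Two people who each keep the same fraction of their strength have the same relative decline, but the weaker one has the lower F_crit.

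The study expects both weakness and higher fatigability in CKD. As the measure is written, the first expectation can produce the second on its own. A lower F_crit in CKD could then be reported as greater fatigability when it only restates the baseline strength deficit. The same ambiguity enters any correlation of F_crit with FACIT-F or MFI-20, because weakness may itself go with perceived fatigue.

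**Working it through.** **Inputs from the article (Statistical analysis):** strength difference 8%, with ±16% read as the SD; 110 per group; alpha 5%, taken as two-sided.

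**Assumed, not in the article:** the fraction of MVC retained at the asymptote has mean f = 0.60 in both groups and between-subject SD s = 0.06 to 0.15, independent of MVC. This is the null case of no difference in relative decline.

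**1. The plan's own figure.** SE = 16 × √(2/110) = 2.157; z = 8/2.157 = 3.708; power = Φ(3.708 − 1.960) = 0.960. The stated 96% reproduces, which supports reading 16% as the SD.

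**2. F_crit under equal relative decline.** Set mean MVC to 100 in controls and 92 in CKD. Mean F_crit is 0.60 × 100 = 60.0 and 0.60 × 92 = 55.2, a difference of 4.8, again 8%. If s = 0, the difference and the SD both shrink by the factor f, so the standardized difference stays at 0.5. The test then rejects in the same 96% of trials.

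**3. With variation between subjects.** Var(F_crit) = f² × 16² + s² × (μ² + 16²), and f² × 16² = 92.16.

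| s | Var, controls | Var, CKD | SE of difference | z = 4.8/SE | Rejection |
|---|---|---|---|---|---|
| 0.06 | 129.08 | 123.55 | 1.516 | 3.17 | 89% |
| 0.09 | 175.23 | 162.79 | 1.753 | 2.74 | 78% |
| 0.12 | 239.85 | 217.73 | 2.040 | 2.35 | 65% |
| 0.15 | 322.92 | 288.36 | 2.357 | 2.04 | 53% |

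Simulation of 4,000 trials per row agrees to within one or two points. Log F_crit adjusted for log baseline MVC rejects in 5 to 6%, as a valid test should. With the sexes pooled (60% male as in the unit; male-to-female strength ratio 1.6, assumed), rejection for unadjusted F_crit falls to about 35 to 55%, because sex adds variance.

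**4. Raw-scale decline does not settle it.** With the same 40% loss, controls fall by 40.0 units and CKD by 0.40 × 92 = 36.8. That difference is significant in 32 to 78% of simulated trials, in the opposite direction: CKD looks less fatigable.

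**5. The simple ratio is not safe everywhere.** Suppose F_crit = 30 + 0.3 × MVC in both groups, with residual SD 6 to 12 (all assumed). The ratio is 60/100 = 0.60 at MVC 100 and 57.6/92 = 0.626 at MVC 92. F_crit/MVC then rejects in 31 to 67% of trials, with the weaker group scored as less fatigable. Log F_crit adjusted for log MVC stays at 5 to 6%.

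**The case against.** - **No unit is printed.** The article does not call F_crit absolute, and Fig. 2 is not shown. The full protocol may plot the curve as a percentage of baseline. This stands: the unscaled reading is the natural one from the text, but it is an inference.
- **The decline is analysed elsewhere.** The course of MVC is the first secondary item under Aims, and the Statistical analysis section gives it a mixed model or repeated-measures ANOVA. This is partial relief. That analysis is not named as the measure of fatigability, and step 4 shows that on the raw scale it can err the other way.
- **The aims do not promise it.** A reader might infer that separating fatigability from weakness is a stated secondary aim. It is not: the list under Aims names neither F_crit nor fatigability, and its last item links dynapenia to subjective fatigue. The F_crit contrast and the fatigability correlation are expectations in the Abstract and Discussion.
- **The correlations may not be pooled.** A reader might infer that the Pearson correlations will mix cases with controls and so carry a high false-positive rate. The article does not say that they are pooled, gives no group differences from which to compute such a rate, and plans regressions that include sex and age. What stands is that baseline MVC is absent from the listed covariates.
- **Proportionality is assumed.** The 50 to 90% range follows from building F_crit as a fraction of MVC, which the documents do not establish. It illustrates what can happen and is not a known error rate of this trial.

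**Conclusion.** The point holds as a mismatch between definition and measure. As the article is written, F_crit is an end level without reference to baseline, so a group difference in it cannot be read as a difference in fatigability when the groups are expected to differ in strength. Under equal relative decline, and with the retention figures assumed above, a difference is declared in roughly 50 to 90% of trials, fewer with the sexes pooled. The documents do not support saying that the trial's fatigability result will come from weakness alone: scaling in the full protocol would remove the problem, and the true relation of F_crit to MVC is unknown. What is affected is the F_crit comparison and the fatigability–fatigue correlation.

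**What to change.** For the between-group comparison, analyse log F_crit with log baseline mean MVC as a covariate. Report F_crit as a percentage of baseline MVC, and absolute F_crit, as descriptive measures. Relate fatigability to FACIT-F and MFI-20 with adjustment for baseline MVC, group, age and sex, or do so within CKD patients. If the full protocol already scales F_crit to baseline, one sentence in the article is enough.

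No new data are needed. The cost is one extra covariate and a short change to the outcome definition. Two limits should be stated: the percentage is unbiased only if F_crit is proportional to MVC, and measurement error in baseline MVC leaves some residual influence of strength, which averaging three contractions reduces.
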